**Fig. 8 Fig8:**
[figure not shown]
Virtual 1st-person view from VRCET and PCET Situation 5

Moreover, for ecological validity purposes, virtual cocaine paraphernalia, doses, and self-administration will be individualized depending on whether the participant’s main use consists of snorting, smoking, or injecting cocaine/crack. Additionally, audio dialogs from virtual avatars are adapted to both Martinican Creole and metropolitan French speakers (speech script available on request). In addition, in order to increase participants embodiment in VR, i.e., the sense of ownership and agency over the virtual body [50], participant virtual skin color will be personalized on request. Finally, for safety and acceptability purposes, given long lasting carry-over effects that could be expected on substance craving and emotional states post cue-exposure [51], VRCEs will have a 10-min washout period, and VRCET sessions will systematically end with a cool-down relaxing procedure with craving check [29, 52].

##### Memory-focused cognitive therapy—week 3

Following the 2-week VRCET phase, participants involved in the VRCET + experimental arm will receive an intensive 1-week MFCT phase delivered daily from Monday to Friday. The MFCT will be structured in accordance with the “Memory Focused Cognitive Therapy for Cocaine Use Disorder” Therapist Guide [39]. MFCT meetings will essentially consist of 5 sequential components: (1) Cognitive case conceptualization of CUD maintaining processes; (2) Education about cocaine’s cognitive and physical effects; (3) Cocaine-related cue-induction to elicit images and affective responses; (4) Memory reconsolidation procedures; (5) Standard CBT techniques (e.g., behavioral experiments of cocaine-related expectancies and skills for adaptive emotion regulation).

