### Outcomes {12}

Our primary outcome will consist in the decrease of the self-reported cocaine craving as assessed with the French Craving Experience Questionnaire (CEQ; [53, 54]. The CEQ is an 11-item retrospective measure of cocaine craving containing two subscales: craving strength (CEQ-S) and frequency (CEQ-F). Each item is completed by the participants on a 10-point scale, from “not at all” (1) to “extremely” (10). The CEQ has shown good psychometric properties [54]. Means of CEQ-S and CEQ-F total scores will be analyzed. Finally, the CEQ will be administered before treatment (V0), after 2 weeks of treatment (V1; VRCET vs. PCET), post-treatment (V2; VRCET + vs. PCET), and 1-month post-treatment (V3; VRCET + vs. CET). The CEQ-S will be administrated immediately after a 7-min VRE to a cocaine-related situation, with a similar scenario to the CET situation 5 (Table 1) but across different virtual environments, avatars, and item appearances (Fig. 9). The CEQ-F will be administrated retrospectively, targeting the last 14-day period. (Table 4)

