#### Randomization

Eligible patients will be randomized by the research psychiatrist or psychologist in charge of the inclusion visit, using the Research Electronic Data Capture (REDCap) secure web application, in the VRCET + (experimental) or PCET (active control) therapeutic arm.

After randomization, participants will be invited to complete baseline self-reported measures as well as to perform a craving induction task related to primary and secondary research objectives. This craving induction task will consist of three 7-min 30 exposures and will systematically start with one VRE to neutral cues, followed by one VRE and one PCE to a cocaine-related situation. The order of these two exposures to cocaine cues (i.e., VRE thus PCE or PCE thus VRE) will be randomly counterbalanced for controlling for potential cue-induced carry-over effect between one exposure to the other. The exposures’ order sequence generation for each participant will be generated by the research methodologist, using the Research Randomizer secure web application, and provided to the investigator within sealed opaque envelope for the inclusion visit.

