## Assignment of interventions: allocation

### Sequence generation {16a}

The Research Electronic Data Capture (REDCap) secure web application will be used for randomizing participant allocation to the experimental or active control therapeutic arm. The randomization will be stratified per investigation center (UHM or SEH), with an allocation ratio of 1:1 to the therapeutic arms and following a randomly permuted per-block order.

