Further, while comparable to superior effects of VRE over classical exposure methods on craving induction in SUDs have been reported [73, 74], to the best of our knowledge, no study has assessed the specific interest of VRCE over a non-VR cue-exposure approach in a CET context [27]. Our trial design will allow to fill the gaps in the literature by specifically assessing the effects of VR, both as a cue-reactivity exposure and cue-exposure therapy paradigm, on cocaine craving in patients with CUD. Indeed, the effects of VR as a cue-reactivity paradigm (i.e., VRE) on cocaine craving-related reactivity and exposure-dependent characteristics (i.e., sense of presence, ecological validity and cybersickness) will be contrasted to the ones of a non-VR cue-reactivity frame (i.e., pictures-based; PCE) at baseline (T0). On the other hand, the acute benefits of VRCET as a stand-alone CET will be compared to the ones a non-VR cue-exposure therapy frame (i.e., PCET) after 2 weeks of a 10-session treatment (T1). We expect to obtain superior effects of VRE or VRCET over PCE and PCET on craving induction and reduction. This may be explained by the fact that VRE environments are designed to be highly immersive (head-mounted display), interactive, multisensorial and implying 3D environments that can include diversified proximal and distal stimuli adapted to the Martinican participants ecological substance using field [21]. Hence, we hypothesize that higher self-reported sense of presence, ecological validity, and realism levels will be self-reported by participants exposed in our high-immersive VRE, as compared with in PCE. Such findings are consistent with meta-analytic evidence (*N* = 115 studies) showing the significant and medium effect of VR immersive features on sense of presence (*r* = 0.316; [75]). In addition, cue-reactivity studies in smokers and heavy drinkers suggest that sense of presence, ecological validity, and realism in VRE significantly predict [76, 77] and enhance craving induction [26]. Furthermore, there is a consensus on the fact that VRCET, compared to PCET, allows diversified exposure to motor, proprioceptive and 3D cues related with cocaine use that could not be used in vivo for safety purposes [21]. Hence, we believe that, compared to PCE, VRCE will allow for broader generalization of CET benefits (i.e., craving reduction) over the desensitization context, and prevent cue-induced craving rebound (e.g., renewal effect) in CUD [22, 23]. Finally, acceptability studies of VRCET as a stand-alone intervention or adjunct to regular treatment for SUD remain scarce [78–80]. In accordance with the findings by Arissen et al. [78], Skeva et al. [79], and Wray and Emery [80], to guarantee the acceptability of VRCE and VRCET, we focused on designing low-cybersickness VR interfaces, shortening and spacing VRCE sessions, and familiarizing therapy facilitators and patients with VRCET and VR prior to the therapeutic phase.

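### Counterbalancing the V0 VR and picture exposures removes order effects and equal carry-over only; half of any difference in carry-over stays in the VRE-PCE contrast, while the primary CEQ-S baseline gains only a little noise

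*Protocol article*

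**What the plan says.** The Randomization paragraph of Participant timeline {13} describes a V0 craving induction task that "will systematically start with one VRE to neutral cues, followed by one VRE and one PCE to a cocaine-related situation". The order of the two cocaine exposures "will be randomly counterbalanced for controlling for potential cue-induced carry-over effect between one exposure to the other". No other control for carry-over is named there. The order list comes from a different person and tool than the arm allocation: the "order sequence generation for each participant will be generated by the research methodologist, using the Research Randomizer secure web application". For the arms, Sequence generation {16a} says: "The randomization will be stratified per investigation center (UHM or SEH), with an allocation ratio of 1:1 to the therapeutic arms".

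Two other places bear on carry-over. The description of the experimental arm expects lasting carry-over on craving and emotional states after cue exposure, and for that reason states that "VRCEs will have a 10-min washout period". The Discussion says: "We expect to obtain superior effects of VRE or VRCET over PCE and PCET on craving induction and reduction".

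The V0 task has two uses. Patients "perform a craving induction task related to primary and secondary research objectives". Outcomes {12} uses it for the VRE-PCE comparison of craving, mood and self-efficacy, which is the second secondary objective. It also defines one of the two primary scores: "The CEQ-S will be administrated immediately after a 7-min VRE to a cocaine-related situation". From T1 on, the schedule (Table 4) lists this measurement in VRE only. The primary test is an independent t-test on the change from T0 to T2.

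**The concern.** The article credits counterbalancing with something it does not do. With two exposures in one visit, averaging over the two orders cancels whatever both orders share. It does not cancel a difference between what VRE leaves behind for the following PCE and what PCE leaves behind for the following VRE. The affected contrast is one of the two places where the Discussion says the specific effect of VR will be assessed.

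There is a second, smaller consequence. About half the patients give their baseline CEQ-S after a picture exposure to cocaine cues, the other half do not, and the later visits have no such exposure. An order effect at T0 therefore does not cancel from the T0-T2 change.

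**Working it through.** **The plan's figure.** The article gives no sample size for the V0 comparison. The trial total of 54 (27 per arm) is reproduced by a two-sided t-test at alpha 0.05, power 0.95 and d = 1.0, with no dropout allowance. The article says only that the effect is large and gives no dropout rate, so 54 can be neither confirmed nor refuted. This point needs only the 27 per arm.

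**Bias in the V0 contrast.** Let τ be the true VRE-PCE difference, π the period effect, λ_V the carry-over from VRE into the following PCE, and λ_P the carry-over from PCE into the following VRE.

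- VRE first: expected VRE − PCE = τ − π − λ_V
- PCE first: expected VRE − PCE = τ + π + λ_P
- Average of the two orders: τ + (λ_P − λ_V)/2

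The period effect cancels, and so does carry-over when λ_P = λ_V. Otherwise half the difference remains. The documents give no carry-over sizes. The values below are assumptions, in SD of the craving score:

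| λ_V | λ_P | Bias (SD) |
|---|---|---|
| 0.4 | 0.4 | 0 |
| 0.4 | 0.2 | −0.10 |
| 0.4 | 0 | −0.20 |
| −0.4 (first VRE habituates) | 0 | +0.20 |

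**Effect on the test.** I simulated 20,000 trials of 54 patients with no true difference and an assumed within-patient correlation of 0.5 or 0.7. Rejection rates at the 5% level:

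| λ_V / λ_P | Paired test | With period term | First cocaine exposure only |
|---|---|---|---|
| 0.4 / 0.2 | 10-12% | 11-15% | 4.6-5.0% |
| 0.4 / 0 | 29-43% | 30-46% | 4.7-5.1% |

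A period term does not help, because unequal carry-over is not a period effect. The first-exposure comparison is protected because both groups reach it after the same neutral VRE and no cocaine exposure.

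**Precision of the first-exposure comparison.** In SD units its standard error is √(2/27) = 0.272. The paired contrast has √(2(1 − ρ)/54), which is 0.136 at ρ = 0.5 and 0.105 at ρ = 0.7. The first-exposure interval is thus about 2.0 to 2.6 times as wide.

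**Primary CEQ-S.** If order is not blocked within arm, the between-arm difference in the share of PCE-first patients has mean 0 and SD √(2 × 0.25/27) = 0.136, so a 95% range of ±1.96 × 0.136 = ±0.267. Take an assumed order effect of 0.5 SD of the change score:

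- Chance shift in the arm contrast: expected value 0, SD 0.5 × 0.136 = 0.068, 95% range ±0.13 SD
- Variance factor: 1 + 0.5²/4 = 1.0625
- Power: 0.950 to 0.938 at d = 1.0; 0.822 to 0.799 at d = 0.8
- Simulated type I error: 4.8% (5.1% with an order effect of 0.8 SD)

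**The case against.** **Unequal carry-over is not established.** A reader might infer from the Discussion that VRE carries over more, so that the contrast is certainly biased. The documents do not support that. Superior induction by VRE is the hypothesis under test, and the Discussion describes earlier evidence as ranging from comparable to superior. This objection stands: the article makes unequal carry-over plausible, no more.

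**The bias may only be conservative.** If a fixed fraction c of the first response persists, the bias is −c × τ/2. The contrast shrinks by 15% at c = 0.3 and 25% at c = 0.5 (both assumed), and is unbiased when τ = 0. The false-positive rates above need carry-over that differs without a true difference. This stands as a limit on those rates. It does not rescue the counterbalancing claim, since attenuation is also an error and habituation would reverse the sign.

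**The primary outcome.** A reader might infer that order is unbalanced between arms and biases the primary comparison. The article describes a separate order list and centre-only stratification of the arms, but does not say whether the order list is blocked within arm. Even if it is not, order is randomised independently of arm, so the expected bias is zero.

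**The washout.** A reader might also infer that V0 has none. The 10-minute interval is stated in the therapy text and V0 is silent, but the article uses the same term for the V0 VR exposure, and questionnaires follow each exposure. This is unclear, not shown to be absent.

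**Model terms belong in an analysis plan.** That is fair, and their absence here is not the finding. The finding is a sentence in the article that claims too much for counterbalancing.

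**Conclusion.** The point holds for the secondary V0 contrast: counterbalancing does not control unequal carry-over. The remaining bias is half the carry-over difference, 0.10 to 0.20 SD under the assumed values, with its direction unknown. These sizes are illustrations, since the documents give none. For the primary CEQ-S the consequence is minor: chance imbalance and about 6% more variance under an assumed 0.5 SD order effect, with no bias and type I error near 5%. The ±0.13 SD is a 95% chance range, not a maximum and not an expected shift.

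**What to change.** - Replace the statement that counterbalancing controls carry-over with one that it controls order effects only.
- Report the VRE versus PCE comparison from the first cocaine exposure (about 27 vs 27) beside the pooled within-patient one. A period term is not a substitute.
- Include exposure order as a covariate in the CEQ-S primary analysis, or as a sensitivity analysis. The plan has no baseline adjustment to extend, so this means a linear model on the change score in place of, or beside, the t-test.
- Block the remaining order list within arm and centre, if it is not already blocked.
- State whether the 10-minute washout in the therapy text applies to the V0 task.

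The analysis items use data the trial already collects and cover patients already enrolled. The order list is an administrative change. The main downside is the lower precision of the first-exposure comparison. The washout item asks for a statement of current practice. Changing V0 timing now, with recruitment open since May 2023, would create two baseline CEQ-S procedures in one trial.

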#### Experimental or active control therapy (3 weeks)

Participants included will start therapy (experimental or active control arm) within 1 week after the inclusion visit as follows:VRCET + (experimental arm): 2-week phase of 10 VRCET sessions, followed by a 1-week phase of 5 MFCT sessions. The VRCET phase will essentially consist of 40 VRE to a progressive hierarchy of 5 diversified cocaine-related situations. The MFCT phase will be in accordance to the “Memory Focused Cognitive Therapy for Cocaine Use Disorder” therapist guide (for request: [39]), and will consist of cognitive restructuring and memory reconsolidation procedures along with imagery exposure to arousing memories of cocaine use.PCET (active control arm): 3-week phase of 15 PCET sessions. The PCET phase will essentially consist of 60 VRE to a progressive hierarchy of 5 diversified cocaine-related situations.

Both VRCET + and PCET sessions will last 1 h 30 min and will be delivered in an intensive 1:1 intervention format, on a daily basis, from Monday to Friday. The facilitator of VRCET + and PCET may differ, but each patient will have only one facilitator.

#### In and post-treatment measuring times (V1, V2, and V3)

The first measuring time (T1) will take place after 2 weeks of treatment, at the 11th treatment session and prior to start the MFCT (experimental arm) or second PCET (active control arm) phase. This will thus allow for comparing short-term research primary and secondary outcomes between VRCET and PCET, after 10 consecutive sessions of exposure.

The second measurement time (T2) will take place at the end of treatment (week 3), at the 15th and last treatment session. This will thus allow for comparing short-term research primary and secondary outcomes between VRCET + (10-session VRCET and 5-session MFCT) and PCET, after 15 consecutive sessions.

The third and last measuring time (T3) will consist in a follow-up visit taking place 1 month after the end of treatment (week 8). This will thus allow for comparing medium-term research primary and secondary outcomes between VRCET + (10-session VRCET and 5-session MFCT) and PCET, 1 month after 15 consecutive sessions of each therapeutic arm. Patients’ participation will end after this visit.

For each of these measurement times, subjective self-report questionnaires and objectives measures related to research objectives will be administered (Fig. 10).

**Fig. 10 Fig10:**
[figure not shown]
Flow chart for the PICOC study

### Sample size {14}

We calculated a required sample size of 54 participants to randomize with G*Power [64], on the basis of two-tailed independent *t*-tests, to detect large effect from our experimental treatment (VRCET +) over our control therapeutic condition (PCET) in reducing cocaine craving [39, 65], given a 0.05 statistical significance threshold, a 0.95 statistical power, and accounting for potential dropouts in our hospitalized inpatients.

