## Introduction

### Background and rationale {6a}

Cocaine is the second most widely used illicit substance in Europe: its annual prevalence of use reached 1.6% of the French population in 2017 and is sharply superior in overseas regions compared to continental European territories [1, 2]. Moreover, one in 6 cocaine users will suffer from cocaine use disorder (CUD; [3]), with significant impacts on health and well-being [4, 5]. The annual social cost of CUD is high as it is estimated to be of 45,469 G$ in the United States alone [6].

Cocaine craving is considered as a central DSM-5 (Diagnostic and Statistical Manual of Mental Disorders – 5th version; [7]) CUD symptom that can be defined as an obsessive motivation to use, which can be automatically elicited when exposed to cocaine cues [8–10]. Importantly, a meta-analysis of 41 cue-reactivity studies suggests that cocaine craving might be the most intense across substances [11]. Hence, craving-focused therapeutic interventions might be of clinical interest for treating CUD, since cocaine craving is a significant proxy of cocaine use and predicts relapse until 3 months post-treatment [12, 13].

Cognitive behavioral therapy (CBT) for substance use disorders targets, *inter alia*, cognitive, affective, and situational triggers for substance use and is shown to be potentially efficacious in treating CUD (*N* = 13 studies; [14]). Stemming from CBT, cue-exposure therapies (CET) essentially aim to extinguish drug cues-associated responses, e.g., cue-induced craving, through repeated non-reinforced exposures. Nevertheless, CET have shown non-significant to small treatment effects in treating SUD according to meta-analytic evidence [15, 16]. These unfavorable results might be due to cue-exposure parameters that have yet to be fully considered when providing CET [15]. For instance, cue-reactivity research suggests the interest of providing more multisensorial, realistic, and ecologically valid exposure environments for improving exposure to substance cues and inducing higher levels of craving [17]. Thus, improving cue-exposure might be of promising value for CET since craving response to substance cues moderates craving reduction [18] and predicts substance use latency, dependence severity and withdrawal reinstatement in a CET context [19].

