### Methods in analysis to handle protocol non-adherence and any statistical methods to handle missing data {20c}

Given the small target sample size (*n* ≈ 50) and in case of arbitrary pattern of missing data, if applicable, multiple imputations for incomplete multivariate data will be performed on all missing data, using the *Amelia R* package [69, 70]. Our comprehensive imputation *R* code will be made available.

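### The claimed 0.95 power for a large effect with 54 randomised and dropouts covered holds only for an unstated d above 1.0; at the conventional d = 0.8, power is about 82% before any loss

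*Protocol article*

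**What the plan says.** The section Sample size {14} of the protocol article reads "We calculated a required sample size of 54 participants to randomize with G*Power". The calculation is "on the basis of two-tailed independent *t*-tests", the aim is "to detect large effect from our experimental treatment (VRCET +) over our control therapeutic condition (PCET) in reducing cocaine craving", and the conditions are "given a 0.05 statistical significance threshold, a 0.95 statistical power, and accounting for potential dropouts in our hospitalized inpatients". Two references support the effect, but no d, mean difference, SD, dropout rate or evaluable number is given.

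Other sections bear on the figure:

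- Sequence generation {16a} sets 1:1 allocation, so 54 means 27 per arm.
- Statistical methods {20a} makes the primary analysis an independent t-test on change from T0 to T2. For reporting effect sizes, it labels a Cliff's delta above 0.47 as large.
- The missing-data section {20c} begins "Given the small target sample size" and puts that size at about 50.
- The discontinuation section {11b} says that participants who stop are not replaced and that their collected data are analysed. The concomitant-care section {11d} excludes the data of participants who receive outside treatment for cocaine use disorder.

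**The concern.** Test, sidedness, alpha, power and sample size are all stated, and the effect is called only large. A reader will take that word in its conventional sense, d = 0.8. On that reading the stated inputs do not lead to 54, even before dropout.

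What is at stake is how a null result is read. A stated power of 0.95 invites the conclusion that a large benefit has been ruled out with a 5% risk of missing it. If the claim covers only effects above one standard deviation, a null result says much less about effects of 0.8 or 0.9 SD.

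The size of the assumed effect also needs declaring because the comparator is an active exposure therapy built on the same situations. The background {6a} says that "CET have shown non-significant to small treatment effects in treating SUD", and the comparator section {6b} speaks of moderate additional effects of cue exposure over active controls. These statements concern cue-exposure therapy in general, not this contrast. They bear on whether d above 1.0 is plausible and not on the arithmetic.

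**Working it through.** **Inputs from the article.** Two-sided alpha 0.05, power 0.95, independent t-test, 54 randomised {14}; 1:1 allocation {16a}.

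**Inputs assumed, because the article gives none.** d = 0.8 as the conventional large effect, and losses of about 10% and 20%. Lost patients are taken to contribute no information.

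**Formula.** With n evaluable per arm, the degrees of freedom are 2n − 2 and the noncentrality is λ = d·√(n/2). Power is the probability that a noncentral t variable with these parameters exceeds the two-sided 5% critical value in absolute size. This is the method G*Power uses.

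**Step 1: reproduce 54.** The number cannot be recovered uniquely, because d and the dropout rate are both missing. The total evaluable number needed for 0.95 power, and the loss that 54 randomised would then allow (1 − N/54), are:

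| d | N needed | loss that 54 allows |
|---|---|---|
| 0.80 | 84 | not reached |
| 0.89 | 68 | not reached |
| 1.00 | 54 | 0% |
| 1.05 | 50 | 7.4% |
| 1.10 | 46 | 14.8% |
| 1.15 | 42 | 22.2% |
| 1.20 | 40 | 25.9% |

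So 54 fits d = 1.0 with no loss. It also fits d = 1.2 with 25% loss (40/0.75 = 53.3, rounded up to 54), and values in between.

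**Step 2: the conventional large effect.** At d = 0.8 and n = 27, λ = 0.8 × √13.5 = 2.94 on 52 degrees of freedom, and power is 0.822. The normal approximation agrees closely: Φ(2.94 − 1.96) = 0.836. Power of 0.95 needs 42 per arm, 84 in total. A one-sided test would still need 70. Totals near 54 at d = 0.8 appear only when a stated input is weakened: 52 for 80% power two-sided, or 56 for 90% power one-sided.

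**Step 3: the article's own cut-off for large.** Under normality with equal variances, Cliff's delta = 2Φ(d/√2) − 1. Setting it to 0.47 gives d = √2 × Φ⁻¹(0.735) = 0.888. Power at 27 per arm is 0.893, and 0.95 power needs 34 per arm (68). That cut-off is given for reporting results and is not tied to the sample-size calculation.

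**Step 4: losses.**

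| evaluable (per arm) | power at d = 0.8 | power at d = 1.0 | d needed for 0.95 power |
|---|---|---|---|
| 54 (27) | 0.822 | 0.950 | 1.00 |
| 50 (25) | 0.792 | 0.934 | 1.04 |
| 48 (24) | 0.774 | 0.924 | 1.06 |
| 44 (22) | 0.736 | 0.900 | 1.11 |

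A 10% loss leaves 48.6 patients, rounded down here to 24 per arm; unrounded, power at d = 0.8 is 0.780. A 20% loss leaves 43.2, which the 22-per-arm row approximates; unrounded, it is 0.728.

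**The case against.** The strongest reply is that the article never says d = 0.8. Large has no upper limit, and an assumed d of 1.05 to 1.2 with about 7% to 26% loss satisfies every stated input at 54. The two cited sources are not at hand, and the full protocol behind this article may give both numbers. All of this stands, and it rules out three stronger statements that a reader might infer.

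- *That 54 patients do not give 95% power.* This is true at d = 0.8 or 0.89 but cannot be asserted for a d that is not stated.
- *That 54 is the no-dropout number for d = 1.0, so dropouts were not allowed for.* This is one fit among several. The figure of about 50 in the missing-data section does not settle it. It may be 54 rounded, or it may be an evaluable number, in which case it matches d = 1.05 with a 7.4% allowance.
- *That the true type II error is 18% to 26%.* That range is conditional on d = 0.8, and its upper end on an assumed loss of about 20% with nothing recovered. The plan analyses the data of those who stop and foresees multiple imputation, so some information may be kept.

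The reply does not remove the point. The article states a power for an effect described only by a word, and on the ordinary meaning of that word the stated power is not delivered. On the reading that rescues the figure, the assumed effect exceeds one standard deviation, and the article does not say so.

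**Conclusion.** The claim is wrong as written, in a limited sense: 0.95 power is presented as applying to a large effect, but with any dropout allowance it applies only to d above 1.0.

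At d = 0.8 the shortfall is about 13 percentage points before loss (0.95 against 0.82) and about 18 with an assumed 10% loss (0.77). At the boundary implied by the article's Cliff's delta label it is about 6 points (0.89). The d = 0.8 figures rest on the conventional meaning of large, the 0.89 figures on normality with equal variances, and the loss figures on assumed rates.

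The text cannot show which d was used. The finding therefore concerns what the power statement covers and is not proof that 54 was miscalculated.

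**What to change.** Keep 54. In Sample size {14}, state the d used, the SD it refers to (change from T0 to T2, to match the primary analysis), its source, and the dropout rate assumed. Then attach the power to that d. If a 10% loss was assumed, for example: *54 randomised give 95% power for d of about 1.06 or more after 10% loss; for d = 0.8, power is 82% with no loss and 77% with 10% loss.*

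If the d used was above 1.0 and agrees with the dropout rate, the 0.95 figure can stay, with a sentence on why an effect of that size over an active exposure therapy is expected. Withdraw the 0.95 figure only if the d used was not above 1.0.

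The cost is a few lines of text and no extra patients. The power quoted for a conventional large effect becomes less favourable.
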